# Comparison of standard circular stapler anastomosis with or without circumferential suture enhancement in patients with robot-assisted Ivor-Lewis oesophagectomy due to malignant tumours of the oesophagus and oesophagogastric junction—a multi-centre, randomised, superiority study (STITCHES)

**DOI:** 10.1186/s13063-025-08995-4

**Published:** 2025-09-16

**Keywords:** RAMIE, Oesophagectomy, Oesophageal cancer, Oesophagogastric anastomosis, Suture reinforcement, Anastomotic leak

## Abstract

**Background:**

Morbidity due to anastomotic leakage is a major concern in transthoracic oesophagectomy. The aim of this randomised trial is to evaluate whether a circumferential suture reinforcement of the stapled end-to-side anastomosis in robot-assisted minimally invasive Ivor-Lewis oesophagectomy (RAMIE) leads to a reduced incidence of anastomotic leakages in the postoperative course.

**Methods/design:**

This is a multi-centre randomised, double-blind, superiority trial with an adaptive sample size design undergoing RAMIE for malignant tumours. Patients will be randomised 1:1 into two study arms. In study arm A, participants will receive a standard circular-stapled end-to-side oesophagogastric anastomosis, while in study arm B, the anastomosis will have a circumferential suture reinforcement. The primary endpoint is the rate of anastomotic leakage. Secondary endpoints are incision-to-suture time, duration of circumferential suture reinforcement, anastomotic stenosis rate, postoperative morbidity and mortality, and quality of life.

**Discussion:**

This randomised controlled trial will assess the impact of circumferential suture reinforcement of the oesophagogastric anastomosis on short-term outcomes and quality of life of patients undergoing robot-assisted minimally invasive Ivor-Lewis oesophagectomy.

**Trial regsitration:**

DRKS00034787. Registered on 7 October 2024.

**Supplementary Information:**

The online version contains supplementary material available at 10.1186/s13063-025-08995-4.

## Background

In the modern multimodality treatment of oesophageal cancer, oesophagectomy has a fundamental role. However, due to its complexity and invasiveness, it is defined as a high-risk procedure that is associated with a higher morbidity than most other surgical procedures. In Germany, a population-based observational study using administrative data found a nationwide caseload-related in-hospital mortality rate ranging between 12.3% (95% confidence interval: 11.1–13.7) and 20.0% (18.5–21.6) [13]. Recent studies have shown a significant improvement in perioperative outcomes with minimally invasive approaches [11]. As a result, the German guideline for oesophageal cancer from the German Guideline Program in Oncology (GGPO) recommends the use of minimally invasive oesophagectomy (MIE) [5]. Robot-assisted minimally invasive oesophagectomy (RAMIE) is a technical advancement that may lead to further improvements in patient outcomes. Compared with MIE, RAMIE can achieve shorter operative times and better lymph node yield in patients who have received neoadjuvant therapy [18].

Irrespective of the type of surgical approach, the formation of the oesophagogastric anastomosis is critical to the success of the operation, as an anastomotic leakage is associated with significant morbidity and mortality [13, 15]. In Ivor-Lewis RAMIE, three distinct anastomotic techniques are currently in use [15]. The anastomosis can be sutured by hand, stapled in a linear fashion side to side, or in a circular fashion end to side. A recent analysis of a multi-centre international registry on RAMIE revealed that the circular-stapled anastomotic technique is employed in 52% of cases, in comparison to 30% for hand-sewn and 18% for linear stapled anastomotic techniques [8]. The highest anastomotic leakage rate was observed in the robot-assisted hand-sewing group (33%), while lower rates were noted in the circular stapling (17%) and linear stapling (15%) groups. These relatively high rates are in contrast with the average incidence of anastomotic leakage of 6.2% reported in a meta-analysis comparing RAMIE with open oesophagectomy [6].

In order to reduce the incidence of anastomotic leakage, different techniques of anastomotic reinforcement have been proposed in the past, including the use of tissue sealant, omental flap and additional suture reinforcement [2, 16, 17].

In Ivor-Lewis RAMIE, the additional use of sutures for reinforcement has been proposed as a crucial measure to reduce leakage rates in end-to-side oesophagogastrostomy performed with the conventional circular stapler technique [6]. However, no studies have yet investigated the potential advantages of supplementary suture reinforcement in terms of anastomotic healing outcomes in robot-assisted Ivor-Lewis oesophagectomy.

Given the above, we aim to investigate whether a circumferential suture reinforcement of the circular-stapled anastomosis (study arm B) is superior to the standard anastomosis without reinforcement (study arm A). The primary endpoint is the rate of anastomotic leakage. Secondary endpoints include incision-to-suture time, duration of circumferential suture reinforcement, anastomotic stenosis rate, postoperative morbidity and mortality, and quality of life.

## Methods

### Aim of the study

This study aims to investigate whether a circumferential suture reinforcement of the standard circular-stapled end-to-side oesophagogastric anastomosis in patients undergoing Ivor-Lewis RAMIE for oesophageal cancer can lower the incidence of anastomotic leakages and thereby reduce postoperative morbidity and mortality. The primary objective of the study is to evaluate the potential for a significant reduction in the rate of anastomotic leakage. It is hypothesised that this will influence secondary outcomes, including postoperative morbidity, mortality and quality of life, but not the rate of anastomotic stenosis.

### Trial design, study registration and ethics

The STITCHES trial is designed as a randomised controlled multi-centric, two-arm parallel-group superiority surgical trial with a control group (study arm A: RAMIE with circular-stapled end-to-side oesophagogastric anastomosis without circumferential suture reinforcement) and an interventional group (study arm B: RAMIE with circular-stapled end-to-side oesophagogastric anastomosis with circumferential suture reinforcement).

The study is coordinated by the leading study centre of the Department of Surgery, University Hospital Erlangen, Germany. The study was initiated at the Department of Surgery, University Hospital Erlangen. It is anticipated that additional centres will be evaluated for participation, if it can be demonstrated that equivalent surgical standards (RAMIE procedure with equal technique) and trial management can be guaranteed at these sites. This trial was registered in advance at the German Clinical Trials Register (DRKS00034787, https://drks.de/search/en/trial/DRKS00034787) on 7 October 2024.

The study protocol was approved by the Ethical Committee at the Friedrich-Alexander-University Erlangen-Nuremberg (24–205-B). Any modifications to the protocol will require a formal amendment. Proposed amendments will be subject to further evaluation and approval. The principal investigator will notify participating centres and will provide a copy of the revised protocol to the responsible investigator. An update of the trial register will be initiated.

The trial will be conducted in line with the Declaration of Helsinki in its current version and with the laws and declaration of the concerned country. In accordance with the Medical Association’s Professional Code of Conduct, the Ärztliche Berufsordnung of each participating German state, an independent Ethics Committee (IEC) must be consulted prior to the commencement of the clinical study in order to address any questions pertaining to professional ethics and legal issues associated with the study. To this end, the study protocol, patient information sheet and informed consent must be submitted to the responsible Ethics Committee.

The study is designed according to the SPIRIT 2013 statement [4]. The SPIRIT checklist was applied and a SPIRIT figure (Fig. 1) was generated.

**Fig. 1 Fig1:**
[figure not shown]
Schedule of enrolment, interventions and assessment according to SPIRIT

### Eligibility

To be able to participate in this study, patients must fulfil several inclusion criteria and be checked for exclusion criteria. These are listed below.

#### Inclusion criteria

All patients scheduled for elective Ivor-Lewis RAMIE for malignant tumours (adenocarcinoma and squamous cell carcinoma) of the oesophagus and oesophagogastric junction are eligible for inclusion. Further inclusion criteria are as follows: intrathoracic circular-stapled end-to-side oesophagogastrostomy, oesophageal carcinoma and carcinomas of the gastrooesophageal junction (Siewert type 1 and 2), age ≥ 18 years.

#### Exclusion criteria

Patients who are not capable of providing informed consent, pregnant or breastfeeding individuals, conversion to open surgery and malfunction of the stapler.

#### Withdrawal criteria

Patients may withdraw from the trial at any time without providing justification. Exclusion from the trial will occur in cases where RAMIE is not performed, for instance, due to technical irresectability, conversion to conventional resection or metastatic disease. However, the withdrawal and reasons will be documented in the patient file and the CRF (case report form), and a CONSORT flow diagram will be provided to ensure comprehensive transparency.

### Interventions

#### Surgical technique

To preclude the potential for learning-associated bias, surgeons with the requisite proficiency will be permitted to perform the randomised interventions. Surgeons participating in the trial as the responsible surgeons must have a minimum of 20 RAMIEs of personal operative experience. This threshold is based on the lower variance range of the learning curves for RAMIE, as determined in a recent systematic review [14]. It should be noted that the standard technique and surgical instruments may vary in several aspects. Nevertheless, the following guidelines have been defined for the present study to reduce the impact of performance bias:The abdominal and thoracic parts of the procedure are performed robotically.A circular, end-to-side oesophagogastrostomy is performed after gastric tube pull-up via a muscle-sparing mini-thoracotomy.A circular stapler with a size range of 25–29 mm is employed.The gastric conduit stump is closed with a linear stapler, with the shortest distance between the linear and circular stapler lines being at least 1 cm.Randomisation is conducted intraoperatively, after the completion of the oesophagogastrostomy.The circumferential suture reinforcement (study arm B) may be performed in an interrupted or continuous fashion with resorbable material (e.g. PDS 4–0, V-loc 4–0). Any type of surgical stitching technique or suture pattern is allowed, provided that the entire circular stapler line is addressed. In case of interrupted suture technique, the number of sutures required is dependent upon the size of the anastomosis.No additional measures to reinforce the anastomosis (e.g. omental flap, pleural flap) are permitted.The placement of drains is at the surgeon’s discretion.Patients do not receive a gastric tube.Perioperative complications associated with oesophagectomy are treated according to current best practices and clinical standards.

### Assignment and randomisation

Patients who have been screened and deemed eligible will be included in the trial following the provision of written informed consent. Randomisation will be conducted intraoperatively, after the completion of the oesophagogastrostomy and verification of the exclusion criteria. The randomisation lists were generated by block randomisation (block size 10) by a computer-based random number generator using the R statistical package (version 4.4.1). The lists were incorporated into the REDCap randomisation tool. The randomisation process will be conducted by authorised trial personnel using the electronic REDCap system.

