### Trial visits

A total of four trial visits will be conducted throughout the course of the trial. During the initial screening visit (visit 1), inclusion criteria and two out of four exclusion criteria will be evaluated. Once the patient has provided informed consent, the following patient characteristics are documented: basic demographic data, comorbidities, the modified frailty index (mFI), American Society of Anesthesiologists (ASA) and Eastern Cooperative Oncology Group (ECOG) scores, as well as tumour-specific parameters. Furthermore, patients are required to complete questionnaires assessing their preoperative quality of life. Quality of life will be evaluated using the aforementioned EORTC questionnaires, depending on the tumour localisation.

The second visit (visit 2) is scheduled for the day of surgery. Once the oesophagogastrostomy has been completed and none of the remaining two exclusion criteria (conversion and malfunction of the stapler) applies, the patient will be randomised using the REDCap randomisation tool. Intraoperative parameters will be collected, including incision-to-suture time, additional suture time for the anastomosis (study arm B), characteristics of the used stapler and intraoperative transfusions of packed red blood cells. Furthermore, the surgeon’s subjective intuition (subjective risk assessment) regarding four postoperative complications (anastomotic leak, conduit necrosis, chyle leak and recurrent laryngeal nerve injury/palsy) will be assessed.

The third and fourth study visits (visit 3 = 30 days postoperative and visit 4 = 6 months postoperative) may be conducted either as part of standard follow-up visits or by telephone. Visit 4 is considered to be part of the standard oncological follow-up. This encompasses a CT scan of the thorax and abdomen, in addition to an esophagogastroduodenoscopy, should clinical symptoms of dysphagia be observed. The primary and secondary endpoints, along with any serious adverse events (SAEs and AEs), will be evaluated and documented during each visit on the case report form (CRF). Data from patients with stapler malfunction, conversion to open surgery or inoperability will be documented until the time of the operation (visit 2). During visits 1 and 4, the standard blood tests (including haemoglobin concentration, leucocyte count and serum C-reactive protein) will be carried out and documented.

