#### Blinding

The STITCHES trial is a double-blind study. As it is not feasible to blind the surgeon, the patients and the follow-up investigators are blinded. The case report forms, which can be viewed by the follow-up investigators, do not specify which study arm the patients belong to. To ensure impartiality, the postoperative study visits are not carried out by the surgeon.

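### A single published block size of 10, with an unblinded operator, lets a team that sees its whole list know some late-in-block allocations before randomisation

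*Protocol article*

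**What the plan says.** Under Assignment and randomisation the article states that "The randomisation lists were generated by block randomisation (block size 10) by a computer-based random number generator", and that the lists sit in the REDCap randomisation tool, operated by authorised trial personnel. The Abstract gives the ratio: "Patients will be randomised 1:1 into two study arms". No other block size is mentioned, and the article does not say whether lists are separate by centre, stratified or shared.

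Under Blinding: "As it is not feasible to blind the surgeon, the patients and the follow-up investigators are blinded".

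On timing: "Randomisation will be conducted intraoperatively, after the completion of the oesophagogastrostomy and verification of the exclusion criteria". Trial visits makes clear what is still open in theatre: the patient is randomised if "none of the remaining two exclusion criteria (conversion and malfunction of the stapler) applies". Some operative choices also precede the draw. Surgical technique, for instance, allows a range of stapler diameters: "A circular stapler with a size range of 25–29 mm is employed".

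The article is dated 16 September 2025. Trial status gives first enrolment on 28 November 2024 and expects recruitment to end in October 2026, so the block size became public during recruitment. The trial began at one centre, with more anticipated (Trial design, study registration and ethics).

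**The concern.** Randomising after the anastomosis is complete is a strong feature of this design. The operator should build the anastomosis, and settle whether the patient has been converted or the stapler has failed, without knowing the arm. The benefit depends on the next arm being unpredictable. With blocks of one known size, anyone who has counted the allocations so far knows the rest of a block as soon as one arm has used its five places.

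An operator who expects no reinforcement could, even unconsciously, take more care over the staple line or judge a borderline malfunction differently. The analysis could not fully undo this. A patient excluded before randomisation never enters the analysed set, so intention-to-treat does not recover that patient. The planned logistic regression can adjust for stapler diameter, which it names, but not for unrecorded care in construction.

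**Working it through.** **The plan's own figure.** The article gives no figure for predictability. Its one computed design figure, about 525 per arm for 17% against 11%, reproduces: [1.960·√(2·0.14·0.86) + 0.842·√(0.17·0.83 + 0.11·0.89)]² / 0.06² ≈ 524. It plays no part in this point.

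**Inputs.** Block size 10 (Assignment and randomisation); ratio 1:1, so 5 A and 5 B (Abstract). Assumption: the observer knows the block size, knows where blocks start and has seen every earlier allocation on the list.

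**Allocations known with certainty.** There are C(10,5) = 252 equally likely sequences. Allocation k is certain when all five places of one arm fall among the first k−1, which has probability 2·C(k−1,5)/252.

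| Position | Calculation | Certain in advance |
|---|---|---|
| 1 to 5 | 0/252 | 0% |
| 6 | 2·1/252 | 0.8% |
| 7 | 2·6/252 | 4.8% |
| 8 | 2·21/252 | 16.7% |
| 9 | 2·56/252 | 44.4% |
| 10 | 2·126/252 | 100% |

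The sum is 420/252 = 1.67 per block, or 16.7%. The closed form agrees: with m = 5, 2m/(m+1) = 10/6. Over the first 100 patients on one fully observed list that is about 17 allocations.

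**Guessing the arm that is behind.** Expected correct guesses per block are m + (4^m/C(2m,m) − 1)/2 = 5 + (1024/252 − 1)/2 = 6.53, or 65.3%. This rule needs only the running count of A and B. It works because blocks return to balance, and it needs neither the block size nor its publication.

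**If the operator sees only part of the list** (simulation, assuming cases are split at random between surgeons):

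| Share of list seen | Certain | Guessed correctly |
|---|---|---|
| All | 16.7% | 65.3% |
| Half | 0.5% | 57% |
| One third | 0.07% | 55% |

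**Effect of varying the block size.** Simulated with sizes drawn at random with equal probability, and an observer who sees the whole list and knows the set of sizes but not their order:

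| Sizes | Certain | Best guess correct |
|---|---|---|
| 10 only | 16.7% | 65.3% |
| 6, 8, 10 | 1.6% | about 66% |
| 8, 10, 12 | 1.3% | about 65% |
| 6, 8, 10, 12 | about 0.9% | about 65% |

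The formula gives the same message for guessing the arm that is behind: (4.10 + 5.33 + 6.53 + 7.72)/36 = 23.68/36 = 65.8% for the four-size mix. Varying the size removes nearly all certainty and leaves general predictability where it was.

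**The case against.** The design is already well protected. The arm is drawn at the latest practical moment, and the next assignment cannot be read from REDCap. The technique rules narrow what an operator can vary. Conversions and stapler failures are recorded with reasons and will appear in a CONSORT diagram, so exclusions could be compared with the allocation that was next in line. Ten is a fairly large block: by the same formula, fixed blocks of 4 or 6 would leave 33% or 25% of allocations certain. Nothing in the article suggests that surgeons count allocations or would act on a guess.

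All of this stands and keeps the point small. It does not remove it. REDCap hides the next entry but not the entries already revealed to an unblinded operator, and recording exclusions permits a check without preventing the conduct.

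The objection also rules out two stronger readings. A reader might take the 65% as a consequence of the published fixed size; it comes from the running balance and would be the same if the size had been kept secret. A reader might also conclude that allocations in general are open to the surgeon. Even under full observation five in six are not certain, and with half the list observed almost none are.

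**Conclusion.** The point holds as a minor, avoidable weakness. A single block size of 10, made public during recruitment, lets a team that follows its whole list know up to 16.7% of allocations in advance on average, all of them in positions 6 to 10 of a block. That figure is an upper bound. It assumes full sight of one list and known block starts, which is plausible at a single starting centre or with lists by centre. It falls steeply if surgeons see only their own cases. The article does not say which applies.

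The documents do not support a claim that concealment has failed or that the leak comparison is biased. No effect on the leak rate has been estimated, and the proposed mechanism is possible rather than observed.

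**What to change.** For the unused part of the current list, and for the lists of any new centres, generate allocations with randomly varying block sizes, for example a mix of 6, 8, 10 and 12. Withhold the sizes from sites and from public documents until recruitment ends. State in the protocol whether lists are kept by centre.

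The gain is a fall in fully determined allocations from at most 16.7% to about 1%, even if the set of sizes becomes known. The change should not be justified by the 65% guessing figure, which it leaves unchanged.

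The cost is one new set of R-generated lists loaded into REDCap. Fixed tens on a single list give exactly 50 per arm at the 100-patient interim. With the mix, an unfinished block can leave the arms slightly unequal: on one list, by at most six patients (half of the largest block, 12/2), plus any imbalance from a block of ten cut short at the changeover. Allocations already made cannot be repaired.

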### Objectives

#### Primary endpoint

The primary endpoint of this study is defined as anastomotic leakage (any type), as described by the Esophagectomy Complications Consensus Group [10]. A separated and pooled analysis (type 1, type 2, type 3 and types 1, 2 and 3) will be conducted.

The primary hypothesis is that the circumferential suture reinforcement of the oesophagogastrostomy will result in a reduction in the rate of anastomotic leakage in Ivor-Lewis RAMIE patients.

#### Secondary endpoints

Secondary endpoints include incision-to-suture time, duration of circumferential suture reinforcement, anastomotic stenosis rate, postoperative morbidity and mortality according to the Clavien–Dindo classification (CDC), and quality of life. Perioperative complications associated with oesophagectomy are recorded in accordance with the ECCG definitions.

Postoperative morbidity with CDC grade ≥ 3b will be the secondary safety endpoint. Quality of life (QoL) is assessed using the EORTC QLQ-C30, EORTC QLQ-OES18 and EORTC QLQ-OG25 questionnaires [1, 3, 9], provided by the European Organisation for Research and Treatment of Cancer.

